## Abstract

**Background:**

Although adolescents are often referred to residential treatment centres because of severe externalizing behaviours, a vast majority demonstrated comorbid symptoms of depression and anxiety. Covert internalizing symptoms in these adolescents might be easily unrecognized and therefore untreated. Adolescents with mild intellectual disability (MID) are overrepresented among youth with both externalizing and internalizing problems. There are yet few treatment programs available for adolescents with both externalizing and internalizing problems.

**Methods/design:**

The CBT-based resiliency program, Op Volle Kracht (OVK), which is based on the US Penn Resiliency Program (PRP), was adapted to suit the needs of adolescents with both externalizing and internalizing problems, either with or without MID, in Dutch residential treatment centres. The effectiveness of this group intervention program of eight sessions will be tested in a randomised controlled trial (RCT) with N = 182 adolescents aged 12–16, allocated to either the target intervention plus treatment as usual (OVK + TAU) or treatment as usual only (TAU). The main outcome variables include depressive symptoms (primary), anxiety, behavioural problems, and group therapeutic climate. Cognitive styles and coping styles will be included as possible mediators. Assessments take place at baseline (T1), one week before the start of the program (T2), immediately after the program (T3), and at three months follow-up (T4).

**Discussion:**

The program assets include its wide implementation possibilities due to low costs, the short duration of the program and the delivery by group care workers, and its suitability for adolescents with MID. Further strengths of the present study design include its robust method (RCT), the ecological validity, and the inclusion of possible mediators of treatment effect. The program emphasizes individual risk factors for depression rather than social and family factors. Implications for practice and future research are discussed.

**Trial registration:**

Dutch Trial Register NTR4836

## Background

In the Netherlands, approximately 25,000 children and adolescents receive residential treatment in the youth welfare system (11,000), youth mental health care (9300) and care for youth with intellectual disabilities each year (5700) [1]. Residential treatment offers 24-h care, including housing, education, and leisure time, in which the daily living environment is used as a therapeutic means. In addition, most institutions offer formal psychological therapy such as cognitive behavioural therapy (CBT) or family interventions, although usually the daily living environment is considered the main therapeutic context [2, 3].

Youth receiving residential treatment are often referred to treatment for severe externalizing behavioural problems (e.g., physical and verbal aggression, disobedience, temper tantrums, hyperactivity, and impulsivity) [4]. Research shows that a large proportion of youth not only have externalizing problems, but also display elevated levels of internalizing problems, such as symptoms of anxiety, depression, and somatization, or have increased risk of developing internalizing disorders such as depressive disorder and anxiety disorder [5, 6]. Moreover, adolescents with both externalizing and internalizing problems more often have MID (e.g. IQ between 50–85) [7, 8]. In these complex cases, more covert, inwardly directed internalizing symptoms may be easily overlooked and given low priority in treatment planning. This might be reflected in treatment outcomes: meta-analyses examining treatment effectiveness show that residential treatment is less effective for internalizing problems than for externalizing problems (effect sizes of .45 and .60, respectively) [9].

Adolescents with comorbid internalizing problems are more severely impaired and have more academic problems, more severe somatic complaints, more problems related to substance use, and poorer overall functioning than adolescents with externalizing problems alone [10–12]. Moreover, youth with a combination of internalizing and externalizing problems have a higher prevalence of suicidal ideation and suicide attempts [13–15]. Longitudinally, comorbid internalizing and externalizing problems are associated with higher rates of adult criminality and higher service utilization rates and costs in adulthood [16]. Thus, underdiagnosis – and therefore undertreatment – of comorbid internalizing problems can lead to further adverse consequences in terms of adolescents’ level of impairment from a long- and short-term perspective.

The high rates of comorbid internalizing and externalizing problem behaviour stress the need for a systematic approach to reduce internalizing problems among youth in residential treatment settings, instead of focusing mainly on externalizing problems. Recent meta-analyses suggest that cognitive-behavioural interventions targeted at emotional resilience for adolescents can significantly reduce internalizing symptoms and decrease the risk for future internalizing symptoms compared to control groups [17–19].

However, most cognitive behavioural interventions are targeted at youth without comorbidities and are insufficiently adapted to youth with complex problems that often are too disorganized in terms of coping with daily life stress, family problems, school problems, etc., to benefit from formal CBT programs. Moreover, to date there are no Dutch CBT programs targeted at youth with MID. This is surprising, given the high rates of youth with MID in residential youth care (>20 %) [1] and the above-average rates of internalizing problems among youth with MID [8]. It is now generally accepted that, due to the social, emotional, and cognitive problems involved, youth with MID require an adapted approach in CBT, including simplified language, smaller steps, and extra emphasis on generalisation to the living environment [20]. Furthermore, most cognitive-behavioural interventions ought to be delivered by specialized health care professionals, such as psychologists and psychiatrists, and therefore do not sort with tendencies in Dutch society toward a more efficient and cost-effective mental health care system with interventions delivered by trained nurses or group workers.

In response to these problems, the existing evidence-based Penn Resiliency Program (PRP) was strongly adapted to (1) suit the needs of the target group, both for adolescents with and without mild intellectual disabilities, and (2) to maximize accessibility by keeping implementation costs low. PRP is a theory-based universal school-based depression prevention program designed for early adolescents (ages 10–14 years) that teaches cognitive-behavioural and coping skills and is one of the most successful programs to increase emotional resilience and to prevent depressive developmental outcomes. Positive results from this program are found in an evaluation of 17 controlled studies evaluating PRP with 2498 participants in total [17]. Recently, PRP has been adapted and translated to fit the Dutch situation, resulting in the creation of the program Op Volle Kracht (OVK, ‘at full strength’). The CBT component of OVK was found to be effective in reducing depressive symptoms in selective samples of girls with elevated levels of depression [21] and adolescents with parents with psychopathology [22]. For the aim of the present study, the OVK program has been adapted to suit the needs of the target group and to suit delivery by nurses and social workers in residential treatment settings.

### Goals and hypotheses

The aim of the present study is threefold: (1) to test the effectiveness of OVK within the usual treatment program (OVK + TAU) in reducing symptoms of depression (primary outcome) compared to treatment as usual alone (TAU), (2) to identify mechanisms that can explain program effects (cognitive bias, coping skills), and (3) to test the effects of OVK on secondary outcomes (anxiety, behavioural problems, and therapeutic climate). It is hypothesized that OVK + TAU will be more effective in reducing symptoms of depression in youth than TAU alone, immediately after the program and at three months follow-up. Regarding the explanatory mechanisms, it is hypothesized that OVK + TAU will decrease negative cognitive biases and increase the adequate coping styles. Both of these constructs are expected to mediate the hypothesized effect of OVK on symptoms of depression. Concerning the secondary outcomes, the OVK program is expected to decrease anxiety, since the program contains cognitive and behavioural strategies that are hypothesized to be effective not only for depression, but also for anxiety (e.g., to recognize and challenge threatening interpretations of neutral events, to employ relaxation strategies [23]). A positive effect on behavioural problems is expected, because behavioural problems are believed to be mediated by deficits in internal impulse regulation and poor self-control [24]. If adolescents learn and adopt cognitive techniques to more adequately regulate their levels of anxiety, they will possess a higher level of self-control to regulate their behaviour, eventually leading to a decrease in problem behaviour. Lastly, the responsiveness of group care workers is hypothesized to increase more in the OVK + TAU group than in the TAU group alone. In the TAU+OVK condition, group care workers will be trained in therapeutic skills necessary to correctly implement the program, including listening skills, conversational skills, and techniques to increase group cohesion. These factors are hypothesized to increase the perceived responsiveness of group care workers.

## Methods

The study design will be reported in accordance with the CONSORT 2010 statement for reporting parallel group randomised trials. The medical ethics committee CMO Region Arnhem-Nijmegen, The Netherlands, has approved the study: NL-49211.091.14.

### Design

This study is an open cluster randomised controlled trial with two conditions: the OVK condition incorporated into the usual treatment (OVK+TAU) versus treatment as usual alone (TAU) (see Fig. 1). There is no comparison condition with another program, because (1) there is no Dutch program suitable to increase emotional resilience in a residential group setting, and (2) internationally, there is no evidence-based alternative for the current program. Therefore, the control condition is a correct reflection of ‘treatment as usual’ within residential treatment settings.

**Fig. 1 Fig1:**
[figure not shown]
Study design

Randomization will be conducted by an independent statistician of the Radboud University Nijmegen and will take place on the level of the naturally existing treatment groups rather than on the level of individuals (clustered randomization). In the Netherlands, residential treatment groups usually comprise 8–10 adolescents that follow the same treatment program, live in the same building, and are usually taken care of by a permanent staff of nurses and social workers. The benefits of randomisation of natural groups are as follows: (1) it minimizes contamination among adolescents and staff; (2) it best reflects the natural situation in residential treatment settings, increasing the ecological validity of the study; (3) adolescents who will receive the intervention program know each other already and are used to undertake therapeutic activities together; and (4) staff members who will conduct the program already have a therapeutic relationship with the adolescents. Stratification on the cognitive level (MID versus non-MID) will be needed in order to ensure that the cognitive level is evenly distributed across the control and intervention conditions.

To test the effectiveness of the intervention, all adolescents and their parents will complete self-report questionnaires approximately one month before the start of the program and before adolescents know to which condition they are assigned (Baseline, T1), approximately one week before the start of the program (T2), immediately after the program (T3), and three months after the end of the program (T4). Adolescents in the control condition will complete the questionnaires at exactly the same time points. To make sure that all adolescents (MID and non-MID) understand the questionnaires, adolescents will be assisted in filling out the questionnaires by a trained research assistant that is blind to condition.

The OVK program will be added to the existing treatment program at the participating groups. The 8-week program will be delivered every week by the permanent staff members at the treatment group who has received training specifically for this purpose. By incorporating the program in the standard treatment program at the groups, we maximize the likelihood that all adolescents can attend sessions, and we minimize stigmatization or social exclusion. To minimize attrition rates, adolescents who are dismissed before the end of the program will be given the opportunity to continue the program at the treatment group. The trial is registered at the Dutch Trial Register: NTR4836. The time frame for the data collection will be from October 2014 until March 2015.

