### Participants and procedure

An a priori power analysis revealed that a sample of N = 182 would be necessary to obtain a power of .8. Three large institutes for residential treatment, including Pluryn De Hoenderloo Groep (youth care), Pluryn Jan Pieter Heije (care for youth with intellectual disability), and Karakter child and adolescent psychiatry (youth mental health care) will participate in this study. All treatment groups with adolescents between 12 and 16 years old, boys and girls, with a full-scale IQ of 50 or higher will be invited to participate. There are 20 treatment groups with 8–10 adolescents each that meet these criteria, of which are 8 youth care groups (Pluryn De Hoenderloo Groep), 8 groups for youth with MID (Pluryn Jan Pieter Heije), 2 mental health care groups, and 2 mental health care groups for youth with MID (Karakter child and youth psychiatry). Five groups (40–50 adolescents) include only boys, three groups (24–30 adolescents) include only girls, and twelve groups (96–120 adolescents) include both boys and girls. If the participants in the groups agree to participate, they will receive more information about the program and training, and the CDI-2 will be administered as a baseline assessment for depression (T1). Subsequently, groups will be randomly allocated to either one of both conditions. From the treatment groups selected, none of the adolescents will be excluded in order to avoid stigmatization and social exclusion. All parents will receive a letter with information regarding the goals and content of the study and will be asked permission for their child’s participation by passive informed consent. Since not all parents may understand written Dutch, given the expected social and ethnic characteristics of the sample, group care workers will ask the parents if they have understood the letter and if they have any questions. Parents and adolescents are free to withdraw themselves from the study at any time. Next, 2–3 permanent staff members of groups allocated to the intervention condition will receive a three-day training conducted by two experienced and licensed psychologists with broad expertise in cognitive behavioural therapy. Subsequently, T2 will be administered, and the training program will start.

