The hypotheses will be tested with mixed effects linear regression analyses in Mplus6. Because adolescents are nested within groups and groups are nested within locations, a three-level analysis is most appropriate to account for the non-independence of the data. However, this technique requires relatively large numbers of clusters (~25) and members in clusters (~25) [45]. With 3 locations, 20 clusters, and 8–10 members in each cluster, a multilevel analysis is not suited. To correct for the problem of the potential non-independence of the data for the clusters, the TYPE = COMPLEX procedure in Mplus will be used. This procedure corrects the standard errors of the parameter estimates for dependency. These standard errors are unbiased estimates and will be greater in comparison to the standard errors derived from individual level analysis. The effect of location will be tested by introducing dummy variables in the regression equation. We will check for possible baseline differences between the two conditions in background variables (e.g., age, sex, and ethnic background, cognitive capacities) and depressive symptoms. These variables will be entered as covariates in the regression equation.

To explore the mediating role of adolescents’ cognitive styles, coping styles, and therapeutic climate, mediation analyses will be performed using Mplus. The significance of indirect paths will be tested via bootstrap sampling. Moderating effects of age, gender, and treatment setting on the relation between depression and anxiety will be explored by entering the moderating variables as predictors for depression/anxiety. The moderation and mediation analyses will be done for the OVK and TAU conditions separately. Reporting of the results of the study will be in accordance with the CONSORT statement [46].

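### Allocation is stratified by MID level but not by institute, although the analysis adjusts for location; randomising within the four institute-by-MID cells would avoid an expected 8–14% variance inflation

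*Protocol article*

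**What the plan says.** The Design section states that randomisation "will take place on the level of the naturally existing treatment groups rather than on the level of individuals (clustered randomization") and is done by an independent statistician. The only stratification factor it names is cognitive level: "Stratification on the cognitive level (MID versus non-MID) will be needed in order to ensure that the cognitive level is evenly distributed". It gives no block size or split rule.

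Participants and procedure lists the groups: "There are 20 treatment groups with 8–10 adolescents each that meet these criteria, of which are 8 youth care groups", then "8 groups for youth with MID" from the intellectual disability institute, and from the psychiatry institute "2 mental health care groups, and 2 mental health care groups for youth with MID". It places the T1 assessment before allocation.

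Statistical analyses counts 3 locations and 20 clusters ("With 3 locations, 20 clusters, and 8–10 members in each cluster, a multilevel analysis is not suited") and says "The effect of location will be tested by introducing dummy variables in the regression equation". Cognitive capacities are among the background variables to be checked and adjusted for: "age, sex, and ethnic background, cognitive capacities) and depressive symptoms. These variables will be entered as covariates in the regression equation".

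Implications for practice states that the program is to be tested in all three Dutch residential youth care settings.

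**The concern.** Location is treated as important in the analysis but left to chance in the allocation. MID stratification indirectly keeps the two large institutes near balance, because each lies within one MID level. It does not control the four psychiatry groups. Once location dummies are in the model, an uneven split of those groups makes arm partly predictable from location, and the treatment effect is estimated less precisely.

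If all four psychiatry groups fall in one arm, they contribute nothing to the location-adjusted contrast. The trial then has no within-psychiatry comparison, despite the aim of testing the program in all three settings. The moderation and mediation analyses are planned separately by condition, so one of them would contain no psychiatry participants. With only 20 clusters, losing the contribution of four is noticeable.

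**Working it through.** **Inputs from the article.** There are 20 groups: 8 youth care (taken as non-MID), 8 MID, 2 psychiatry non-MID and 2 psychiatry MID. Each MID stratum is therefore 10 = 8 + 2. Nominal power is 0.80 at one-sided alpha 0.05.

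**Assumptions.** Each MID stratum is split exactly 5:5, clusters are of equal size, the three locations are the three institutes, and cognitive level, where used, is coded MID yes/no.

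**The plan's own figure.** It gives no figure for allocation balance. Its sample size reproduces: 102 × 1.49 = 152, and 152 × 1.2 = 182.4, the stated 182. The nominal 0.80 is the starting point below.

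**Step 1: allocation probabilities.**
- Both psychiatry groups of a stratum in the same arm: 2 × C(8,3)/C(10,5) = 112/252 = 4/9 = 44%.
- In at least one stratum: 1 − (5/9)² = 56/81 = 69%.
- All four in one arm: 2 × (2/9)² = 8/81 = 9.9%.
- An 8-group institute wholly in one arm: impossible, since each arm takes only 5 groups per stratum. Its split is never worse than 3:5.

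**Step 2: variance inflation, 1/(1 − R²)**, where R² comes from regressing the arm indicator on the adjustment terms. The total sum of squares is 20 × 0.25 = 5. Let u and v be the number of psychiatry groups in the intervention arm in each stratum, minus 1.

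- *Location dummies alone:* explained sum of squares = (u² + v²)/8 + (u + v)²/4.
- *Location dummies plus binary MID* (which together saturate the four cells): explained sum of squares = 5(u² + v²)/8.

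| Psychiatry split | Probability | Location alone: R², inflation | Location + MID: R², inflation |
|---|---|---|---|
| Even in both strata | 25/81 | 0, 1.000 | 0, 1.000 |
| Uneven in one stratum | 40/81 | .075, 1.081 | .125, 1.143 |
| Uneven in both, opposite arms | 8/81 | .05, 1.053 | .25, 1.333 |
| Uneven in both, same arm | 8/81 | .25, 1.333 | .25, 1.333 |

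Expected inflation:
- Location alone: (25 × 1 + 40 × 1.081 + 8 × 1.053 + 8 × 1.333)/81 = 1.078.
- Location + MID: (25 × 1 + 40 × 1.143 + 16 × 1.333)/81 = 1.136.

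**Step 3: power.** Power = Φ((1.645 + 0.842)/√inflation − 1.645). Averaged over the table, 80% becomes 77.4% (location alone) or 75.5% (location + MID). At the maximum inflation of 1.333 it is 69%.

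**Step 4: institute-by-MID strata.** The cells of 8, 8, 2 and 2 are all even, so they split 4/4, 4/4, 1/1, 1/1. R² is 0, inflation is 1.00, and no institute can lie wholly in one arm. The number of possible allocations is 70 × 70 × 2 × 2 = 19,600, against 252² = 63,504 with MID strata only, so over-stratification is not a worry.

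**Step 5: if groups decline.** Mean inflation in 4,000 simulated allocations per scenario (location alone / location + MID):

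| Missing groups | MID strata | Institute-by-MID strata |
|---|---|---|
| One psychiatry | 1.084 / 1.146 | 1.018 / 1.056 |
| One youth care | 1.092 / 1.157 | 1.008 / 1.008 |
| One from each large institute | 1.104 / 1.173 | 1.016 / 1.016 |
| One psychiatry per MID level | 1.093 / 1.157 | 1.062 / 1.125 |

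The finer strata were better in each case. In the last row little is gained, and the one-arm risk for psychiatry stays near 50% under either scheme.

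**The case against.** MID-stratified cluster randomisation is valid and unbiased over repeated allocations, and nothing in the article contradicts itself here. The planned covariates (location, background variables, depressive symptoms) largely deal with chance imbalance between institutes. A reader might infer that the comparison will be confounded by institute. The article does not support that: location is adjusted for, and no depression levels by institute are given. What adjustment cannot restore is a psychiatry comparison when all four groups sit in one arm.

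A reader might also take 14% as the unconditional cost. It needs location dummies and a binary MID term together. The article mentions cognitive capacities without saying how they are coded, and IQ scores are also collected. With location dummies alone the figure is 8%, and 1.33 then arises in 9.9% of allocations, against 20% (16/81) with both terms.

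The power figures give no credit for variance that the covariates explain, so they are not forecasts of actual power. The relative loss against institute stratification remains.

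Finally, that MID is the sole factor is read from no other being named in a condensed article, and the 5:5 split is assumed; independent coin tosses would make the one-arm probability 12.5%. That caveat stands. Still, the article does state its stratification factor and the reason for it, so the point concerns a stated choice. If the full protocol already stratifies by institute, the point falls away.

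**Conclusion.** The point holds as an avoidable loss of efficiency, not as a threat to validity. The size depends on the final covariate set, hence the 8–14% range. The 9.9% event is already included in those averages and must not be added to them, and it concerns the psychiatry institute alone. In 31% of allocations (25/81) there is no loss at all. The conclusion rests on the group counts in the article, exact 5:5 splits, equal cluster sizes and all 20 groups taking part. Because the remedy is close to free, it is worth making even for a loss of this modest size.

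**What to change.** Have the independent statistician randomise within the four institute-by-MID cells (4/4, 4/4, 1/1, 1/1), and keep institute and MID as fixed effects in the primary model. MID stays balanced automatically, because the cells lie within MID levels. If a group declines and a cell becomes odd, allocate the odd groups together within their MID level; balance is then close but not exact.

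The cost is a short change to the randomisation specification before allocation. No participants or visits are added, and the location dummies are already planned.
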